### **3.7 PKIDS Engagement Core**

The PKIDS Engagement Core will establish recruitment and membership criteria for patients to participate as members of the PKIDS PFP. The members of the PKIDS PFP are not research participants, but rather partners in research. The PKIDS Engagement Core will develop and implement the strategic plan to increase patient and caregiver partners and stakeholder engagement in PKIDS, including: 1) recruiting PFP members at other PKIDS sites that accurately represent the broad spectrum of patients and families served by these institutions and 2) leveraging ongoing patient/participant engagement efforts at each PKIDS site to recruit PFP members. The PKIDS Engagement Core will consist of PKIDS team members from four organizations: CHOP and 3 sites that rotate yearly.

### **3.8 Clinician Council**

The Clinician Council is a group of providers who care for patients with stones (for example, urology, radiology, nephrology) and represent the geographic locations, provider ages, and experience levels in PKIDS. The Council will provide strategic and tactical input about the study from front-line clinicians, review PKIDS site

---

---

practice patterns, and serve as experts in the engagement with clinicians in the community of practice.

### **3.9 Private Sector Advisory Group**

The Private Sector Advisory Group includes, for example, payers and companies that make equipment used for stone surgery. This Advisory Group will continue to identify areas of common interest and offer suggestions for how to work more effectively with one another to improve patient care. The members of this group may expand as the study progresses.

---

## **4 STUDY PROCEDURES**

Please see Table 1 and 2 (p. vi).

### **4.1 Screening Visit**

Review of the electronic health record for potentially eligible patient participants will occur before consent is obtained.

- Electronic health record review
  - Date of birth
  - Past medical history
  - Past surgical history
  - Comorbidities
  - Clinician notes

### **4.2 Consent**

- a. Patients participants who are not hospitalized will be contacted before or at a clinic visit or on the day of surgery to inform them about the study. When feasible, patients who present to the ED will be included. Screened patient participants may be contacted by telephone or in-person to obtain consent. The informed consent process for in-person consent may occur at ambulatory clinic visits, inpatient hospitalizations, in the ED, or on the telephone. Patient participants can be enrolled either in-person or via telephone up to and including the day of surgery before the procedure. Only patients with a sufficient amount of time to consider study participation will be approached. On day of surgery no pre-medications which may impact their ability to consent or assent will be distributed prior to consent.
- b. Surgeon participants will be approached before identifying patient participants. They will provide consent/assent (waiver of documentation) via REDCap by clicking on an “I Agree” button to then continue to complete the questionnaire.

### **4.3 Participant Questionnaires**

All study participants will complete questionnaires.

#### **4.3.1 Questionnaires**

Patient participants will complete a baseline questionnaire that assesses individual characteristics, including but not limited to past medical history and family history, with particular emphasis on stone factors. Patient participants will complete questionnaires, including PROMIS measures and a urinary symptom questionnaire, before surgery (baseline), within 7 days of surgery (+/- 3 days), 21-days +/- 7-days, 45-days +/- 7-days, and 90 days +/- 30 days after surgery. The questionnaires include, but are not limited to, PROMIS instruments (pain intensity, pain interference, anxiety, psychological stress experiences) and a urinary symptom questionnaire. Questionnaires will be administered electronically and recorded in secure electronic databases including OnCore and REDCap, enabling completion at

---

---

home. For patients who do not have mobile devices or a computer, a member of the research team can administer the questionnaires over the phone or on paper.

Surgeon participants will complete one time questionnaires assessing individual and institution characteristics via REDCap.

#### **4.3.2 Ultrasound (as part of clinical care)**

As part of routine clinical care, patient participants will undergo an ultrasound 6 weeks (+/- 2 weeks) after surgery. The results of the ultrasound will be obtained via medical records/imaging review.

#### **4.4 Operative Summary**

At the end of the surgical case, the attending surgeon will complete an operative summary. The summary will contain details about the stone and technical details of the procedure and may be administered electronically or on paper. The results of the summary will be recorded in OnCore and/or REDCap by a member of the study team.

#### **4.5 EHR Surveillance**

Patient participant data from ED visits, hospitalizations, clinic visits, and surgical (re)treatment will be obtained during the duration of clinical follow-up in PKIDS. A member of the research team at each site will manually access the data at the PKIDS site and enter it into the secure electronic database (e.g. OnCore). For the 8 PEDSnet sites, outcomes will also be ascertained by querying the PEDSnet Common Data Model at each PEDSnet site. Patient participants may be contacted to verify information obtained about healthcare encounters that occurred within 3 months of the index surgical procedure.

#### **4.6 Unscheduled Visits**

This study does not involve any study visits; all visits are for clinical care. Unscheduled visits that are part of clinical care will be recorded. Unscheduled visits that are specific to the study are not expected. Should one occur, the PI will be notified and will ascertain the reason for the visit and ensure that all questions have been answered. Any AEs, which are not expected, will be noted and reported.

#### **4.7 Subject Completion/Withdrawal**

Participants may withdraw from the study at any time without prejudice to their care. The reason for withdrawal will be recorded. It will be documented whether or not each participant completes the clinical study. If investigator(s) become aware of any serious, related adverse events after the participant completes or withdraws from the study, those events will be recorded in the source documents.

##### **4.7.1 Early Termination Study Visit**

Participants who withdraw from the study will have all procedures enumerated for the study visit as the early termination visit.

---

---

---

---

## **5 STUDY EVALUATIONS AND MEASUREMENTS**

### **5.1 Monitoring Evaluations and Measurements**

There are three major data sources that will be used for analysis: (1) EHR of patient participant, (2) patient participant report, and (3) surgeon report.

#### **5.1.1 Screening**

Before consent is obtained, a member of the research team will use the EHR to assess for patient eligibility. A diverse population with respect to sex, race, geography, and comorbidities will be included, thereby assuring representation of the full spectrum of patients with stones in the US.

#### **5.1.2 Medical Record Review (Baseline) and EHR Surveillance (during duration of follow-up at each site)**

The variables that may be obtained from the medical record at baseline include, but are not limited to, the following:

- Date of birth
- Weight
- Height
- Race and ethnicity
- Sex
- Past medical history, include specialty and acute care utilization
- Past surgical history, including operative reports
- Family history
- Medications
- Diagnoses
- Healthcare payer
- Diagnostic imaging

The EHR will be surveilled for clinic visits, ED visits, unplanned hospitalizations, and surgical retreatment. Data from institutions in PEDSnet may be obtained using an automated data pull. Research team members at each site may manually abstract the data and enter it into REDCap and/or OnCore.

### **5.2 Participant Questionnaires**

Patient participants will complete questionnaires that include PROMIS measures, quality of life instruments, and a urinary symptom questionnaire. These questionnaires will be administered before surgery (baseline), within 7 days of surgery (+/- 3 days), 21-days +/- 7-days, 45-days +/- 7-days, and 90 days +/- 30 days after surgery. The questionnaires may be distributed electronically or administered over the phone or on paper. The baseline questionnaires may be completed at any time between enrolling in the study and the surgery, including the day of surgery before the procedure.

---

Based on patient interviews, the anticipated PROMIS profile may include pain intensity, pain interference, anxiety, psychological stress experiences, peer relationships, and family relationships. The PFP will approve the final profile. All questionnaires will be administered and recorded in REDCap.

Surgeon participants will complete one time questionnaires via REDCap assessing individual and institution characteristics.

### **5.3 Operative Summary**

The attending surgeon will fill out an operative summary that includes a questionnaire regarding the kidney stone and operative techniques used during the kidney stone surgery immediately after the procedure is finished. These items include:

- 1) Procedure type
- 2) Lithotripsy method
- 3) Energy settings, if applicable
- 4) Ancillary equipment such as stents, catheters, or drains
- 5) Operative findings
- 6) Intra-operative imaging parameters, if applicable

The surgeon can complete an electronic or paper version of the summary, and the results will be stored in OnCore. The PKIDS surgeons will be trained on how to use the summary in order to ensure standardization of the reporting. Ultimately, a templated version of the summary could be developed in the EHR that will include information from the checklist.

### **5.4 Ultrasound**

Stone clearance will be assessed with an ultrasound (as part of clinical care) 6 weeks (+/- 2 weeks) after surgery, which is the current standard of clinical care at all sites. Radiologists at PKIDS sites will document findings in radiology reports. Coordinators will abstract standardized radiology reports and record results in OnCore. Ultrasound images coded with a PKIDS ID for all CHOP will be uploaded to Arcus.

To assess and improve inter-observer reliability, a random sample of ultrasounds will be reviewed centrally by a pediatric radiologist blinded to the surgery. Images coded with the PKIDS ID will be uploaded remotely to CHOP's Arcus data research infrastructure. Arcus will provide a secure, cloud-based platform to receive, store, and analyze these images. Please see Section 7 for details about Arcus data security and confidentiality. Centralized review will occur more frequently in the first 6 months of the study to allow for quality assessment and improvement.

---

---

Discrepancies between local and central interpretations will be reconciled and the reasons for any discrepancy will be identified to improve ultrasound interpretation across PKIDS.

### **5.5 Surgeon and site characteristics**

In addition to the participant-facing measurements described below, urologists at PKIDS sites will complete questionnaires via REDCap about their surgical training, operative experience, preferences for particular kidney stone surgeries, access to kidney stone surgical equipment, techniques used during surgery, and importance of secondary factors related to surgery for children (e.g. radiation exposure, need for ancillary procedures, hypertension). In addition, they will provide information about the resources and environment of their healthcare system, including ownership of surgical equipment and relationships to lithotripsy centers.

## 6 STATISTICAL CONSIDERATIONS

### 6.1 Primary Endpoint

Stone Clearance

### 6.2 Secondary Endpoints

Patients' Experiences.

### 6.3 Control of Bias and Confounding

While all patients meeting eligibility criteria may be enrolled, we will restrict analysis to the first kidney stone surgery to avoid introducing clustering at the patient-level for the few (likely more complex) patients who would have multiple stone events over the 21-month enrollment period. Considering the large number of potential confounders, a pre-specified list of characteristics that includes but is not limited to the variables in Table 2 will be ascertained before surgery.

| Patient-level                         | Surgeon-level                                                                  |
|---------------------------------------|--------------------------------------------------------------------------------|
| Patient demographics                  | Years of out of residency                                                      |
| Body mass index                       | Experience with SWL, URS, and PCNL                                             |
| Pain at stone presentation            | Endourology fellowship                                                         |
| Insurance type                        | Pediatric urology fellowship                                                   |
| Number of stones                      | Preferences for URS, SWL, and PCNL                                             |
| Type of stone                         | Ownership in SWL collaborative                                                 |
| Single location vs. multicentric      | Ownership of surgery center                                                    |
| UTI at presentation or history of UTI | Surgeon gender                                                                 |
| Neurogenic bladder                    | Preferences for particular surgery                                             |
| Urinary tract anomaly                 | Importance of factors in surgery choice (radiation, reimbursement, discomfort) |
| Expectations about surgery            |                                                                                |
| Prior urinary tract reconstruction    | Hospital-level                                                          |
| Hydronephrosis                        | Hospital characteristics (e.g. bed number, nursing staffing)                   |
| Co-morbid conditions                  | Annual number of URS, SWL, PCNL performed at the hospital                      |
| Prior kidney stone surgery            | Interventional radiology available                                             |
| Acute/urgent procedure or elective    | SWL machine owned by hospital                                                  |
| Prior diversion for the stone episode | Laser ownership                                                                |
| Ambulatory status                     | Kidney Stone Center                                                            |
| Pre-op imaging type                   | Trainee involvement in surgery                                                 |
| Pre- and post-operative medications   | Free-standing children's hospital                                              |

We will construct propensity score models based on these confounders, and use an inverse probability treatment weighting approach for multi-level data to balance covariates across treatments at patient- surgeon- and hospital-levels in evaluation of overall treatment effect and HTE. As we compare three treatments, we will use multinomial logistic regression with random effects to calculate propensity scores. The random effects will allow us to account for correlation within surgeon- and hospital-levels. We assume there is overlap among the treatment groups such that every patient could have received each treatment. Under this assumption, the weighted treatment effects yield consistent estimates of the population averaged treatment effects, provided that the commonly assumed assumptions of consistency

and no unmeasured confounders in causal inference also hold. We will examine overlap of covariates across treatment groups using plots of distributions of the estimated propensity scores across groups, and examine the balance of covariates using standardized difference in mean before and after weighting. We will also conduct sensitivity analyses using both simulation-based approaches and propensity score-based sensitivity functions to assess the effect of potential unmeasured confounding on the estimates of the parameters of interest.

## Statistical Methods

The statistical methods will be described in detail in the Statistical Analysis Plan.

### 6.3.1 Baseline Data

Baseline and demographic characteristics will be summarized by standard descriptive summaries (e.g. means and standard deviations for continuous variables such as age and percentages for categorical variables such as gender).

### 6.3.2 Analysis of Primary Outcome of Interest

**Stone Clearance: Overall Treatment Effect** The primary analysis of Aim 1 is to test the differences in stone clearance after surgery across treatment options. We will fit weighted logistic regression models for stone clearance measured at 6 weeks after surgery. We will use the likelihood ratio test to test the null hypothesis. We will report point estimates and 95% confidence intervals (CIs) of odds ratios in stone clearance between each pair of treatments.

**SubAim 1a: Heterogeneity of Treatment Effect (HTE).** We will add pairwise interactions between the treatment dummy variables and stone size and between treatment and stone location. We will also explore HTE by other patient participant characteristics including, but not limited to, ambulatory status.

**SubAim 1b: Effect modification by procedure-specific techniques.** We will stratify the data by treatments and, within each treatment, we will fit logistic regression models with random intercepts to test whether modifiable techniques improve stone clearance.

### Patient Experiences: Overall Treatment Effect.

For PROMIS measures, we will fit weighted linear mixed effects models to test the difference in T-scores after surgery across treatment options for each domain. Separate models will be built for outcomes at 1 week, 3 weeks, 6 weeks, and 3 months after surgery. We will also take advantage of the longitudinal nature of the PROs and fit WLMMs to compare the slopes of the PROs over time and the area under the curve.

Secondary patient experience outcomes, including number of emergency department visits, unplanned hospitalizations, and surgical retreatment will be compared across treatment options using weighted zero-inflated negative binomial regression models.

**SubAim 2a: HTE.** We will examine for HTE with interaction terms between procedure and patient age and procedure and sex to identify associations that differ for subgroups. We will also explore HTE by other patient participant characteristics including, but not limited to, ambulatory status.

**SubAim 2b: Effect modification by procedure-specific techniques.** We will stratify the data by treatments and, within each treatment; we will fit linear mixed effect models to test whether modifiable techniques are associated with patients' experiences for each procedure.

We will evaluate the change in outcomes across PKIDS after knowledge of best practices generated by the above analyses are integrated into clinical care. Our regression models will test differences in both the intercept (average value) and slope (change over time) for outcomes.

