Up to 60% of children with kidney or ureteral stones (hereafter referred to as kidney stones) require surgery. As for adults, surgery is indicated when a ureteral stone does not pass and for non-obstructing kidney stones that are too large to pass, cause infection, pain, or hematuria, and when patients choose treatment over surveillance. Surgical options include ureteroscopy (URS), shockwave lithotripsy (SWL), and percutaneous nephrolithotomy (PCNL), all of which use an energy source to break stones and require anesthesia. URS is an outpatient endoscopic surgery that accesses the ureters and kidneys per the urethra to fragment and remove the stones. SWL is a non-invasive outpatient procedure that targets stones in the kidney or ureter with x-ray or ultrasound and uses shockwaves generated outside the body to fragment them; the fragments pass down the ureter and the patient expels them in the urine. PCNL is a minimally invasive surgery in which a ~1cm flank incision is made, and a scope is passed through a tubular sheath into the kidney to fragment and remove the stone. There is typically a 1- to 2-night hospital stay. Many patients who undergo URS, SWL, or PCNL also have temporary tubes placed after the surgery to facilitate drainage, either internally (a stent) or externally (a nephrostomy tube). Proper treatment selection, which is directed by patient-specific factors and individual treatment goals, is the greatest determinant of successful outcomes.

Stone clearance is a surgical outcome that is important to patients because residual stone fragments lead to painful stone passage, ED visits, and surgical retreatment. The comparative effectiveness of URS, SWL, and PCNL with respect to stone clearance for pediatric patients is unclear because of five characteristics of prior studies.

- Biased measurement of stone clearance due to use of multiple imaging modalities with different sensitivities.
- Combining patients who had repeated treatments with those who had one treatment in a single group.
- Heterogeneity of the size of residual stone fragments after surgery considered “clinically insignificant”.
- No consideration of factors impacting treatment choice and outcomes (*e.g.*, surgeon characteristics).

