### 2.2 Secondary Objectives (or Aim)

The secondary objective is to compare patients' experiences after URS, SWL, and PCNL. We will assess the immediate (within 7-days +/- 3 days) and delayed (21-days +/- 7-days, 45-days +/- 7-days, and 90 days +/- 30 days) impact of surgery on patient-reported outcomes (PROs) selected by PKIDS patient partners. The PROs include the PROMIS, other questionnaires commonly used in studying the impact of kidney stone disease on health states, and urinary tract symptoms. We will examine HTE by age and sex and identify modifiable surgical techniques that impact these experiences for each surgery. We will also determine unplanned hospitalizations, ED visits, and repeat surgeries for the 3 months following each procedure.

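### ED visits and unplanned hospitalizations are counted from the procedure in every group, so early events managed during the usual PCNL hospital stay go uncounted, while the same events after outpatient URS or SWL are counted

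*Combined protocol and SAP*

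**What the plan says.** **Outcomes and model.** Protocol section 6.3.2, under Patient Experiences: Overall Treatment Effect, states: "Secondary patient experience outcomes, including number of emergency department visits, unplanned hospitalizations, and surgical retreatment will be compared across treatment options". The model is a weighted zero-inflated negative binomial regression.

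**Counting window.** Section 2.2: "We will also determine unplanned hospitalizations, ED visits, and repeat surgeries for the 3 months following each procedure". The clock starts at the procedure in every group. Neither protocol nor SAP says how the index stay is treated, and neither defines an unplanned hospitalization.

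**Care setting.** All three descriptions are in section 1.2. For URS: "URS is an outpatient endoscopic surgery". For SWL: "SWL is a non-invasive outpatient procedure". For PCNL: "There is typically a 1- to 2-night hospital stay".

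**Data collected.** Section 5.1.2: "The EHR will be surveilled for clinic visits, ED visits, unplanned hospitalizations, and surgical retreatment". Section 4.5 is slightly wider, because it collects hospitalizations without restricting them to unplanned ones: "Patient participant data from ED visits, hospitalizations, clinic visits, and surgical (re)treatment will be obtained".

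**Other sources.**
- The operative summary (section 5.3) is completed straight after surgery.
- Table 1 schedules adverse event assessment from 1 week onward. Sections 7.1 and 7.2 provide for monitoring and for reporting to the IRB, with no comparison between procedures.
- The SAP's secondary outcomes are patient-reported outcomes only, so it adds no rule for these counts.

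**The concern.** An ED visit or an unplanned admission can happen only to someone who has left hospital. After URS or SWL that is usually the day of surgery. After PCNL it is typically one or two nights later. Suppose the same problem, such as a fever on the first night, arises with equal frequency after each procedure. After URS or SWL it can produce an ED visit, an admission or both. After PCNL it is managed on the ward and produces neither.

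The difference lies in how the outcome is measured, not in who receives which procedure, so inverse-probability weighting leaves it untouched however well the covariates balance. It affects PCNL versus URS and PCNL versus SWL. URS versus SWL is not affected in the same way, since both are described as outpatient.

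The protocol's stated goal is to help families choose between procedures, and unplanned encounters are part of Specific Aim 1 in the abstract. A result of fewer unplanned encounters after PCNL could arise partly from where patients spend the first nights.

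**Working it through.** The documents give no event rate, power or margin for these outcomes, so there is no planned figure to reproduce. The check has two parts: what each source can record, and how large the effect could be.

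**1. What is recorded if an event arises on the first post-operative night**

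| Source | URS or SWL (at home) | PCNL (in hospital) |
|---|---|---|
| ED visit (2.2, 6.3.2) | counted | cannot occur |
| Unplanned hospitalization (2.2, 6.3.2) | counted if admitted | no new admission; treatment of a prolonged stay not stated |
| Surgical retreatment (2.2, 6.3.2) | counted | an in-stay reoperation may be counted |
| Operative summary (5.3) | completed before the event | completed before the event |
| Adverse event assessment (Table 1, 7.1, 7.2) | no comparison by procedure | no comparison by procedure |

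The gap is therefore confined to ED visits and unplanned hospitalizations during the index stay. Events after discharge are counted in all groups.

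**2. Size under equal true risk**

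Let R be the true risk of an event needing unplanned care, equal in PCNL and URS, and f the share of such events that arise and are managed within the index stay.

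- Counted URS risk = R
- Counted PCNL risk = R × (1 − f)
- Counted PCNL:URS ratio = 1 − f

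The documents give neither R nor f; both are assumptions here.

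*Events spread evenly over 90 days:* f = 1/90 = 1.1% for one night and 2/90 = 2.2% for two. The ratio is 0.989 or 0.978, which is negligible.

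*Events clustered early:* the table also gives the chance of a significant false advantage for PCNL. It uses a two-sided 5% test of two proportions, unweighted, at the planned enrolment in section 6.4 (100 PCNL, 750 URS), before loss to follow-up. The formula is Φ[(d − 1.96 × SE0)/SE1], where d is the difference in counted risk, SE0 the pooled and SE1 the unpooled standard error.

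Worked case, R = 20% and f = 25%:
- counted PCNL risk = 0.20 × 0.75 = 0.15, so d = 0.05
- pooled risk = (100 × 0.15 + 750 × 0.20)/850 = 0.194
- SE0 = √[0.194 × 0.806 × (1/100 + 1/750)] = 0.0421
- SE1 = √(0.15 × 0.85/100 + 0.20 × 0.80/750) = 0.0386
- Φ[(0.05 − 0.0825)/0.0386] = Φ(−0.84) = 20%

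| f (assumed) | Ratio | R = 10%: counted PCNL risk | False advantage | R = 20%: counted PCNL risk | False advantage |
|---|---|---|---|---|---|
| 0 | 1.00 | 10.0% | 2.5% | 20.0% | 2.5% |
| 10% | 0.90 | 9.0% | 4% | 18.0% | 6% |
| 25% | 0.75 | 7.5% | 10% | 15.0% | 20% |
| 50% | 0.50 | 5.0% | 33% | 10.0% | 71% |

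The zero row is the ordinary one-directional error rate. The planned analysis is a weighted count model, so these chances show order of magnitude only.

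**3. Would an exposure offset be enough?** No offset is stated. Removing two of 90 days from PCNL exposure divides the PCNL rate by 88/90 = 0.978, a rise of about 2%. That corrects an even spread of events. It does not correct early clustering, because the days removed are the ones with the most events.

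**The case against.** **These are encounter outcomes, not harm outcomes.** The protocol calls them patient experience outcomes and unplanned healthcare encounters. If a child avoids an unplanned return because he or she was already on the ward, that is a real difference in unplanned encounters. This stands. The counts are valid as utilisation; the problem arises when they are read as comparative safety, and no section says they will be. But no other comparison by procedure of early complications is planned, so that reading is easy to slip into.

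**The blind spot is not total.** A reader might infer that the plan cannot see any in-stay complication after PCNL. The documents do not support that. An in-stay reoperation may count as retreatment, section 4.5 collects hospitalizations generally, and adverse events are monitored throughout. An assessment at 1 week could look back over the preceding days. What is missing is a planned comparison using that information.

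**Early symptoms are measured elsewhere.** QUIKSS covers the past 7 days, including blood in the urine and painful urination, and PROMIS pain scores are compared at 1 week. That is partial cover: these are symptom scores rather than events, and QUIKSS has no fever item.

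**The settings are not absolute.** The PCNL stay is described as typical, not as planned, and section 7.6 allows recruitment of inpatients, so some URS or SWL patients may also be in hospital around surgery. If sites coded a prolonged PCNL stay as an unplanned hospitalization, the gap would shrink; nothing tells them to.

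**The bias may be trivial.** With events spread evenly it is 1% to 2%. This stands as a limit on any claim about size.

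**A composite including prolonged stay could bias the other way.** Such a component would apply mainly to PCNL. eTable 4 also shows more developmental delay in the enrolled PCNL cohort than in URS (39.8% versus 11.9%) and more neuromuscular disorder (35.5% versus 12.3%), which might lengthen stays for other reasons. This stands, and argues for separate reporting.

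**Conclusion.** The point holds for ED visits and unplanned hospitalizations. Followed as written, the plan leaves early events managed within the index stay uncounted after PCNL while counting them after URS or SWL, and weighting cannot repair this. The direction favours PCNL. It rests on section 1.2's description of the usual care settings and on a prolonged stay not being coded as an unplanned hospitalization.

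The size is not known. Under equal true risk the counted ratio is 0.98 to 0.99 if events are evenly spread, and 0.90, 0.75 or 0.50 if 10%, 25% or 50% of events fall within the stay. The last three shares are assumed.

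A reader might go further and suppose that an artefactual safety result would sit beside an established PCNL clearance advantage for large stones. That is not supported. With multiple imputation (eTable 13) the difference for stones over 15 mm is 20.7 percentage points, with a 95% confidence interval from −15.4 to 56.8.

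This concerns a secondary outcome and does not touch the stone-clearance analysis.

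**What to change.** In section 6.3.2, with a matching entry in the SAP:

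1. **Common start.** Add a sensitivity analysis of ED visits and unplanned hospitalizations that begins counting at one post-operative time for all three procedures, for example after post-operative day 2, the upper end of the typical PCNL stay. Keep the count from the procedure as planned and show both.
2. **Definition.** State whether a prolonged index stay counts as an unplanned hospitalization, and apply the rule identically to every procedure.
3. **Separate reporting.** Report index-stay length and unplanned events during the stay by procedure, beside the encounter counts and not merged into them.
4. **Interpretation.** State that the encounter counts alone will not be read as comparative safety.

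**Cost.** The first item is one extra analysis on encounter dates that should already be held through the EHR surveillance. The second is a sentence. The third may need a few more fields from hospital records that coordinators already open. None changes patient care.

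**Downside.** The common start drops early events in every group: 2/90 = 2.2% if they are evenly spread, more if they cluster early. A patient whose stay runs past the common start is still not at risk until discharge, so the correction is incomplete for prolonged stays. The separate stay data show how often that happens.
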